## Abstract

**Background:**

Zygomaticomaxillary complex (ZMC) and zygomatic arch (ZA) fractures are common injuries resulting from facial trauma and frequently require surgical management (Huang et al., Craniomaxillofac Trauma Reconstr 8(4):271-6, 2015). A substantial number of post-operative functional and cosmetic complications can arise from the surgical management of these fractures. These include scarring, inadequate facial profile restoration, facial asymmetries and diplopia (Ellis et al. J Oral Maxillofac Surg 54(4):386-400, 1996; Yang et al. Oral Maxillofac Surg Clin North Am 23(1):31-45, 2011; Kloss et al. Int J Oral Maxillofac Surg 40(1):33-7, 2011). Intuitively, most of these aforementioned complications arise as a result of inadequate fracture reduction; however, current standard practice is to assess reduction post-operatively through plain radiographs or computed tomography (CT) scans. The role of intra-operative CT scanning to assess the reduction of ZMC/ZA fractures and the potential impact on complications, has thus far not been established.

**Methods:**

This is a prospective randomised controlled trial currently being undertaken at the Royal Brisbane and Women’s Hospital. All patients who require operative management of their ZMC or ZA fractures are offered enrollment in the trial. The patients are randomised into two groups: interventional (intra-operative CT) and control (no intra-operative CT). All patients in each group will have post-operative radiographs taken. From these radiographs, the reduction of the ZMC and/or ZA fracture is graded by a blinded assessor. Patients will be reviewed in clinic at 1 week and 6 weeks post-surgery. During these consultations, all patients will be assessed for scarring, diplopia, facial profile restoration and need for revision surgery.

**Discussion:**

Many complications associated with surgical management of ZMC and ZA fractures involve poor aesthetic results as a direct consequence of inadequate fracture reduction. Inadequate fracture reduction is predictable given that small incisions are used and only limited visualisation of the fractures is possible during the procedure. This is due to a desire to limit scarring and reduce the risk of damage to vital structures in an aesthetically sensitive region of the body. It follows that an intraoperative adjunctive tool such as a CT scan, which can assist in visualisation of the fractures and the subsequent reduction, could potentially improve reduction and reduce complications.

**Trial registration:**

Australian New Zealand Clinical Trials Registry, ACTRN12616000693426. Registered on 26 May 2016.

**Electronic supplementary material:**

The online version of this article (10.1186/s13063-019-3625-8) contains supplementary material, which is available to authorized users.

## Background

Zygomaticomaxillary complex (ZMC) and zygomatic arch (ZA) fractures are a relatively common injury in Australia, with the Royal Brisbane and Women’s Hospital managing approximately 160 patients per year [1]. Many of these fractures require surgical reduction and fixation to restore either function or aesthetic form or a combination of the two. Precise reduction of ZA and ZMC fractures can be difficult due to limited visualisation of the fractured bones. Surgical exposure of the fractures is intentionally kept to a minimum to reduce facial scarring and protect vital structures in an aesthetically sensitive region of the body. Current surgical approaches usually produce minimal scarring and provide adequate protection of vital structures; however, as a consequence of this minimalist approach, exposure of the fractures can be very restricted. A potential sequala of minimal fracture exposure is inadequate reduction. This in turn can lead to poor cosmetic results such as facial asymmetry, poor facial profile restoration, facial scarring, limited mouth opening or restricted eye movement [2–4]. It is clearly of the highest priority to surgeons to avoid these potential adverse outcomes.

The current standard procedure for assessing fracture reduction is to perform plain radiography or computed tomography (CT) in the post-operative setting. This provides adequate assessment of the reduction; however, if there are any inaccuracies, correction can only be achieved through a second procedure. With the increasing availability of intraoperative CT, it is surmised that this technology could improve ZMC and ZA fracture reduction and subsequently reduce post-operative complications. To date there are only a small number of studies that have investigated the use of intra-operative CT in the management of ZMC fractures [5–14]. Most of the studies involve small patient sample sizes and none provide level-1 evidence. Many of these studies conclude that intraoperative CT can improve fracture reduction and revision surgery rates. However, to date there have been no randomised controlled trials (RCTs) published to adequately assess this hypothesis.

The aim of this RCT is to assess the use of intra-operative CT in improving radiographic fracture reduction, clinical outcomes and revision surgery rates in the management of ZMC and ZA fractures. Due to the lack of current literature on assessing the potential for use of intra-operative CT, we feel that an RCT will provide an invaluable contribution to the medical literature.

## Methods

### Study objectives

The primary objective of the trial is to determine if intraoperative CT imaging improves clinical outcomes for zygomaticomaxillary complex and zygomatic arch fractures that are managed surgically. This will be assessed through the following variables:
Post-operative radiographic reduction adequacyNeed for revision surgeryNumber of intra-operative re-reductionsPost-operative diplopiaFacial profile restorationSurgical incision and scarring

The secondary objective of the trial is to ascertain whether intraoperative CT imaging has a significant impact on the length of surgery and whether it affects the outcomes of delayed versus early surgical treatment outcomes [15].

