### Evaluation of outcomes

The two-sample *t* test will be used for analysis of continuous variables. The chi-square test will be used for analysis of categorical variables and for all data, a *p* value <0.05 will be considered significant. The software program SPSS will be used for all statistical analysis. Subgroup analysis based on the severity of the fractures will also be conducted. Patients will be analysed as per their treatment but non adherence will be considered in the final presentation of data. An interim analysis will be also be undertaken. There are no other audits of trial conduct planned.

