### Power calculation

An estimated 200 patients will be required for a sample size that will produce significant results. This is based on two-sided testing with a power calculation of 80% and is established from local department outcome estimates and results from studies by Van Hout et al., Hurrell et al. and Van Den Bergh et al. [10, 15, 16]. The variable that required the largest projected sample size to obtain a statistically significant result was the adequacy of post-operative fracture reduction as demonstrated radiographically. The power calculation was performed by [name], a biostatistician from the University of Queensland (UQ) School of Population Health.

Due to the low level of evidence available in the current literature, the sample size calculations may not be reliable and estimates were not possible for all variables being proposed in this study. Subsequently, a mid-study analysis will be conducted to more accurately assess the predicted sample size calculations. It is estimated that from the average number patients presenting yearly with ZMC and ZA fractures at the RBWH, this study will take approximately 2 years to complete. If the mid-study analysis identifies a statistically significant result, the study will potentially be terminated early. The decision to terminate the trial or continue after the mid-study analysis will be at the discretion of the study authors.

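### Six unranked variables carry the primary objective at p<0.05 each: if any one suffices, the chance of a false positive is about 21–26% for correlations of 0.5 to 0, and 80% power cannot be claimed for the objective as a whole

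*Protocol article*

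**What the plan says.** In the protocol article, Study objectives states a single broad aim: "The primary objective of the trial is to determine if intraoperative CT imaging improves clinical outcomes". It continues "This will be assessed through the following variables" and lists six: radiographic reduction adequacy, revision surgery, intra-operative re-reductions, diplopia, facial profile restoration, and incision and scarring. None is ranked or called the primary outcome.

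Evaluation of outcomes sets one threshold: "for all data, a *p* value <0.05 will be considered significant". No adjustment for several tests is mentioned.

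Power calculation says "An estimated 200 patients will be required for a sample size that will produce significant results" and "This is based on two-sided testing with a power calculation of 80" percent. It explains the number this way: "The variable that required the largest projected sample size to obtain a statistically significant result was the adequacy of post-operative fracture reduction". It then adds that "estimates were not possible for all variables being proposed in this study", without saying which. The same section allows early termination, at the authors' discretion, if the mid-study analysis gives a significant result. It ties that result to no variable.

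Blinding and Follow up and outcomes state that the post-operative radiographs are graded blind and that the clinic assessor at 1 and 6 weeks is not blinded.

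**The concern.** A trial needs to fix in advance which result answers its main question. Here six candidates share that role, with no order among them and no rule for combining them. The main claim could therefore be chosen after the data are seen, and each variable adds a chance of a false claim.

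The choice matters more than usual for two reasons.

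- Radiographic reduction adequacy is the only one of the six stated to be assessed blind. Success could be claimed on an unblinded clinic grade alone.
- Re-reductions are partly produced by the intervention. Under Study groups, surgeons in the CT arm review the scan and redo an inaccurate reduction, while controls have no intra-operative imaging to prompt this. A difference is expected there even if patients gain nothing, yet the variable sits under the primary objective.

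On power, a reader may take 80% to hold for the primary objective. For the variables that could not be estimated, a null result would be hard to interpret.

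**Working it through.** **Inputs.** From the article: six variables (Study objectives); 0.05 for each test (Evaluation of outcomes); 200 patients, two-sided testing, 80% power, set by reduction adequacy as the variable needing the most patients (Power calculation). Assumed: one test per variable, one look, one significant variable is enough, all six null hypotheses true, and a common correlation between test statistics, because the article gives none.

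**1. The plan's own figure.** The 200 cannot be reproduced, because no control rate or effect size is given. For illustration only, 100 per arm gives 80% power for 30% v 13.7%, 20% v 6.6%, or 10% v 1.0%. The 200 can be neither confirmed nor called wrong.

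**2. False-positive chance if any one of six suffices.** With independent tests it is 1 − 0.95^6 = 0.265. With correlation, from 600,000 simulated sets of six equicorrelated normal statistics:

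| Correlation | At least one p<0.05 |
|---|---|
| 0 | 26.5% |
| 0.3 | 24.2% |
| 0.5 | 20.7% |
| 0.7 | 16.5% |
| 0.9 | 10.9% |

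Counting only false results in favour of CT gives 14.1% (independent) to 10.4% (correlation 0.5), against 2.5% for one two-sided test.

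If re-reductions are left out because the intervention itself produces them, five independent tests give 1 − 0.95^5 = 0.226.

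**3. Power of the other variables at 200.** A variable that needs N patients for 80% power has, at 200, power Φ((1.960 + 0.842)·√(200/N) − 1.960).

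- N = 200: 80%
- N = 150: Φ(2.802 × 1.155 − 1.960) = Φ(1.28) = 90%
- N = 100: Φ(2.802 × 1.414 − 1.960) = Φ(2.00) = 98%

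Reduction adequacy needed the largest sample of those estimated, so every other estimated variable has at least 80% power under the planning assumptions. For variables with no estimate, nothing can be computed.

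**4. Cost of correcting by Bonferroni instead.** Each test would be at 0.05/6 = 0.0083, with critical value 2.638. Power for the sizing variable at 200 becomes Φ(2.802 − 2.638) = Φ(0.164) = 56%. Restoring 80% needs 200 × ((2.638 + 0.842)/2.802)² ≈ 200 × 1.543 ≈ 309 patients.

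**The case against.** The best defence is that the article states no rule under which one significant variable meets the objective, so any overall error rate is the reviewer's construction. It is also a condensed account, and an analysis plan may settle multiplicity. Part of this stands: 21–26% is conditional and is not a property that the article fixes. The Background attributes poor clinical results to inadequate reduction, so correlations above 0.5 cannot be excluded. But the article is not silent. It gives the list, applies one threshold to everything, and lets an unspecified significant result prompt early stopping. Even at correlation 0.9 the error is about twice nominal.

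Three stronger readings are tempting, and the article does not support them.

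- A reader might infer that the 80% power applies to reduction adequacy alone. Because that variable needed the most patients, the other estimated variables have at least 80% power.
- A reader might infer that revision surgery was never sized. The article does not say which variables lacked an estimate.
- A reader might count nine tests, because three grades are recorded at both 1 and 6 weeks. That would give 27–37% at correlations of 0.5 to 0. The article says patients are assessed at both visits, but not that each visit is tested separately. Repeat grades of the same feature are also likely to be more strongly correlated than that.

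A further fair objection is that choosing a primary outcome after recruitment has begun carries its own risk of bias. It does, and the fix has to deal with it openly.

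**Conclusion.** The point holds in this form: six unranked variables carry one primary objective, each at 0.05, with no primary outcome and no success rule. If any one suffices, the chance of at least one false positive is about 21–26%. This assumes six true nulls, one test each, a single look and correlations of 0.5 to 0. Higher correlation lowers it (16.5% at 0.7, 10.9% at 0.9). The mid-study look is not counted; at an unadjusted 0.05 and an assumed half of the data, it would raise the figure to about 32–41% for correlations of 0.5 to 0.

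The 80% power belongs to reduction adequacy and to whichever other variables were estimated. It is unknown for the rest, so it cannot be claimed for the primary objective as a whole.

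**What to change.** Before any further unblinded analysis:

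1. Name blinded radiographic reduction adequacy as the single primary outcome at two-sided 0.05, and reword the primary objective to match. It already sets the 200 and is the only variable stated to be graded blind.
2. Make revision surgery, diplopia, facial profile and scarring secondary. Take 6 weeks as the time point for the three clinic grades. Either adjust these tests by Holm or label them supportive.
3. Report intra-operative re-reductions as a descriptive process measure.
4. Tie the mid-study significance rule to the named primary outcome.
5. Restate Power calculation as 80% power for reduction adequacy, at least that for any other variable actually estimated (naming them), and unknown power for the rest.

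With one primary outcome the error returns to 5% at a single look; the mid-study look still needs its own threshold.

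**Cost.** No more patients, against about 309 under Bonferroni over six. The authors give up claiming success on a secondary outcome alone, and the headline question narrows from clinical outcomes to radiographic reduction, which is a scientific choice as well as a wording change. Trial status puts the start of recruitment in August 2016, so the amendment must be dated and disclosed as made after recruitment began, and must state whether the mid-study analysis had been seen. The article already undertakes to notify the ethics committee and the registry of amendments.

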### Study design

This is a prospective, single-centre, double-blinded, RCT. It will be conducted by the Oral and Maxillofacial Surgery department (OMFS) at the Royal Brisbane and Women’s Hospital in Brisbane (RBWH), Australia. This is a tertiary teaching hospital and major trauma centre for the city of Brisbane and the state of Queensland. The study was approved by the Royal Brisbane and Women’s Hospital Human Research Ethics Committee (reference number HREC/16/QRBW/18) on 27 July 2016 prior to recruitment of patients. This study complies with the National Health and Medical Research Council’s (NHMRC) National Statement on Ethical Conduct in Human Research (2007). The trial was registered with the Australian and New Zealand Clinical Trials Registry (registration number ACTRN12616000693426) on 26 May 2016 prior to patient recruitment. Please see the Standard protocol items: recommendation for interventional trials (SPIRIT) figure (Fig. 1) for an illustration of the timeline for enrolment, interventions and assessments in the trial. The SPIRIT checklist has been completed for further information (Additional file 1).

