### Blinding

The patients will not be informed of the group to which they are randomised. Concurrently, the clinician assessing the fracture reduction on the post-operative radiographs will be blinded to the arm of the trial to which the patient has been allocated. The surgeon operating on the patient will not be blinded as this is impossible, given they will be witness to whether or not intra-operative CT is performed. The physician assessing the patient in clinic at both 1 week and 6 weeks post-surgery will not be blinded to the patient’s study group. Blinding of this assessment would be extremely difficult as the physician assessing the patient will be involved with the operation and hence know the allocated group. The clinician assessing the post-operative radiographic reduction will not perform any of the operations in the trial.

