### Follow up and outcomes

All patients in the trial will have post-operative SMV, PA face, OM15 and OM30 radiographs taken either on the day of surgery or on the following day, prior to discharge. These radiographs will be assessed blinded to study group, by an oral and maxillofacial surgeon who will not be involved in any of the operations or pre-surgical or post-surgical clinical assessments. The adequacy of the fracture reduction will be based on the radiographs and the quality of the reduction will be evaluated as “good”, “fair” or “poor”:
Good: equivalent to premorbidFair: minor discrepancy but unlikely to require re-operationPoor: major discrepancy, re-operation required

Patients in the trial who are undergoing ZMC open reduction and internal fixation will stay overnight in hospital, and barring any complications will be discharged home on day 1 post-surgery. Patients undergoing open reduction of their isolated ZA fracture will be discharged on the same day as surgery, unless there are any unforeseen complications. All patients will be followed up in the OMFS outpatient department at 1 week and 6 weeks post-surgery. During these outpatient appointments, the registrar or consultant reviewing the patient will assess them for diplopia, surgical site scarring and facial profile restoration. These parameters will be graded by the OMFS registrar or consultant and their assessment will be recorded on a standardised form (Figs. 2 and 3). The need for revision surgery at any timepoint until 3 months following the completion of the study and a number of other variables (see Figs. 2 and 3 for a full list) will also be recorded on the form.

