### Data collection, management and confidentiality

Data from the post-operative radiographic assessments will be entered directly into the trial Excel spreadsheet. All data recorded on the post-operative assessment forms (Figs. 2 and 3) will be transferred to the trial Excel spreadsheet. This Excel file will be stored on a single, password-protected personal computer. At the completion of the trial, the Excel spreadsheet will be transferred to a password-protected computer within the OMFS department at the RBWH. It will be stored on this computer for 15 years. All hard copies of the consent and post-operative assessment forms will be stored in a designated trial folder, which will be stored in a locked room in the OMFS department at the RBWH. At the completion of the trial, this folder will remain in the OMFS department for 15 years. The final trial data set will only be accessible to the authors of the trial.

Data on patients’ names, date of birth, gender, address and occupation will not be collected. Patients will only be identified by their unique record number (URN), otherwise known as a medical record or hospital record number. The URNs will be removed from the data pool prior to statistical analysis.

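### The trial is labelled double-blinded, yet three of the six primary-objective outcomes are graded by a clinician who knows the allocation

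*Protocol article*

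**What the plan says.** The design label in Study design carries no qualification: "This is a prospective, single-centre, double-blinded, RCT". The section on Blinding then sets out four roles.

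- Patients are blinded: "The patients will not be informed of the group to which they are randomised".
- The radiograph reader is blinded. Follow up and outcomes confirms this and adds independence from the surgery: "These radiographs will be assessed blinded to study group, by an oral and maxillofacial surgeon who will not be involved in any of the operations".
- The operating surgeon is not: "The surgeon operating on the patient will not be blinded as this is impossible".
- The clinic physician is not. The person "assessing the patient in clinic at both 1 week and 6 weeks post-surgery will not be blinded". The reason given is that this physician takes part in the operation, so masking would be very hard to arrange.

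Follow up and outcomes says of diplopia, scarring and facial profile: "These parameters will be graded by the OMFS registrar or consultant". All three are among the six variables listed under the primary objective, which reads: "The primary objective of the trial is to determine if intraoperative CT imaging improves clinical outcomes". Evaluation of outcomes applies one significance threshold, p<0.05, to all data. Power calculation says the radiographic variable needed the largest sample. It also lets the authors end the trial early if the mid-study analysis is statistically significant, without saying for which variable.

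**The concern.** The primary objective is framed in terms of clinical outcomes. The outcomes examined on the patient in clinic are graded by someone who knows whether a scan was done, whereas the blinded outcome is an imaging grade. The three clinic grades call for judgement, so knowledge of the arm can shift them without any intent to do so.

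Two things are at stake. A reader who takes the design label at face value will give these comparisons more weight than they can bear. And because the significance threshold and the early-termination clause do not separate blinded from unblinded variables, a difference produced by grading could be reported as a confirmed benefit or contribute to ending the trial.

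**Working it through.** **Step 1: classify the six variables** (Study objectives) by who decides or grades each one (Blinding; Study groups; Follow up and outcomes).

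| Variable | Decided or graded by | Knows the arm? | Could masked grading help? |
|---|---|---|---|
| Radiographic reduction | Surgeon outside all operations and clinical assessments | No | Already masked |
| Diplopia | Clinic registrar or consultant | Yes | Yes |
| Facial profile | Clinic registrar or consultant | Yes | Yes |
| Scarring | Clinic registrar or consultant | Yes | Yes |
| Intra-operative re-reductions | Operating surgeon, after viewing the scan in the CT arm | Yes | No, it is part of what the intervention does |
| Revision surgery | Not named; recorded on the clinic form | Not stated | Cannot be judged from the text |

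One of six is blinded. Four of six are in unblinded hands on the express text. Of those four, three are open to a bias that masked grading could reduce.

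**Step 2: what the plan's own figure provides.** The article states 200 patients, 80% power and two-sided testing, but gives no event rates or effect size, so 200 cannot be reproduced. Only the resulting 100 per arm is used below, taking the two-ball draw as 1:1.

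**Step 3: illustrate what assessor bias could do.** The documents give no rates for the clinic grades, and the forms holding the grading scales are not shown. Everything here except the sample size and the 0.05 threshold is therefore assumed.

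- p: true unfavourable rate, the same in both arms.
- b: share of unfavourable CT-arm results graded as favourable because the arm is known.
- Apparent CT-arm rate p2 = p(1 − b); spurious difference d = p − p2; mean rate m = (p + p2)/2.
- SE0 = √[2m(1 − m)/100]; SE1 = √{[p(1 − p) + p2(1 − p2)]/100}.
- False-positive rate = Φ[(d − 1.96·SE0)/SE1] + Φ[(−d − 1.96·SE0)/SE1], the normal approximation to the uncorrected chi-square test.

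Worked case, p = 20% and b = 30%: p2 = 0.14, d = 0.06, m = 0.17. SE0 = √(2 × 0.17 × 0.83/100) = 0.0531. SE1 = √[(0.16 + 0.1204)/100] = 0.0530. The first term is Φ(−0.83) ≈ 0.202 and the second is about 0.001, so the total is 20.3%.

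| True unfavourable rate | b = 10% | b = 20% | b = 30% | b = 50% |
|---|---|---|---|---|
| 10% | 5.7% | 7.8% | 11.8% | 26.8% |
| 20% | 6.5% | 11.4% | 20.3% | 50.8% |
| 30% | 7.6% | 15.9% | 30.8% | 72.2% |
| 40% | 9.0% | 21.7% | 43.3% | 87.6% |

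With b = 0, as masked grading aims for, the rate is the nominal 5%. The direction is assumed as well: a grader who leaned the other way would hide a real benefit.

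**The case against.** The best reply is that nothing is concealed. The Blinding section names who is and is not masked, with reasons. Two parties are blinded, so the label is imprecise rather than false. The variable that set the sample size is the blinded one and is protected. The article says masking the clinic review would be very hard. Judging one's own work occurs in both arms, so by itself it does not bias the comparison; only knowledge of the arm does.

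Most of this stands, and it limits the point to three outcomes. It does not rescue the label for those outcomes, nor does it limit the p<0.05 rule or the early-termination clause to the blinded variable. The stated difficulty follows from using reviewers who were in theatre. The trial already uses a surgeon outside the operations for the radiographs, so some separation of roles is feasible, although the article does not show that it is for every clinic visit.

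Four stronger readings are tempting and are not supported.

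- *Five of six primary variables suffer avoidable bias.* Re-reduction follows from the scan itself, and masking cannot change that. No one is named as deciding on revision surgery, and the blinded reader's worst grade is itself defined by a need to re-operate.
- *The radiograph reader can see the arm in the shared spreadsheet.* The Data collection section says "Data from the post-operative radiographic assessments will be entered directly into the trial Excel spreadsheet", but not who enters the data, whether the reader can open the file, or whether allocation is visible there.
- *The blinded patients' own ratings are ignored.* The assessment forms are not shown and may contain such items.
- *The inflation can be given as one figure.* No rates or grading scales are available, so any single value is only an assumption.

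**Conclusion.** The point holds for three of the six primary-objective variables. The double-blind label does not describe how diplopia, facial profile and scarring are graded, and those comparisons are open to assessor bias of unknown size and direction. The illustrative false-positive rate runs from about 6% to 50% at a 20% unfavourable rate. Across the whole grid it runs from 5.7% to 87.6%, with the top values needing half of all unfavourable CT-arm results to be misgraded. These figures assume a binary grade, 100 per arm, no true effect and a lean towards CT; they show that the bias could matter, not that it will. The blinded radiographic comparison is unaffected. This should be corrected, but it does not undermine the trial as a whole.

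**What to change.** 1. **Wording and hierarchy.** Describe the trial as patient- and radiographic-assessor-blinded. State that confirmatory claims, and any early-termination decision, rest on the blinded radiographic grade that already set the sample size. Report diplopia, facial profile and scarring as unblinded and supportive. Fix this before results by arm are examined, and notify the ethics committee and the registry, as the article promises for amendments.
2. **Clinic review.** Add a field to the 1- and 6-week form recording whether the reviewer took part in the operation. Where the roster allows, use an existing department clinician who did not. Run a sensitivity analysis of the three clinic grades by reviewer involvement.
3. **Optional precaution, not the repair of a proven breach.** Keep the radiographic grades in a file without allocation or operative data until data lock.

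**Cost.** No change to the sample size and no extra staff; minor rostering effort and one form field. Recruitment began in August 2016, so the field will be missing for patients already followed up unless it can be recovered from operative records. A reviewer from outside theatre may still learn the arm, and the sensitivity analysis compares non-randomised groups of visits, so both reduce the problem without removing it. The main price is weaker claims for the clinic outcomes.
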